### Study procedures and data collection

The primary source of data for the study will be the patient-level medication profiles generated at each community pharmacy. All data will be collected by a research assistant traveling to each pharmacy. Data will be collected using a standardized abstraction instrument. Only data without unique personal identifiers, but with a unique study ID# (and therefore anonymized), will be entered into a secure database housed at the EPICORE Centre, University of Alberta. Investigators will be blinded to physician- and patient-level unique identifiers and investigators and study patients will be masked to allocation status. Primary care physicians themselves cannot be blinded to allocation status. Follow-up data collection is scheduled at 6-months, again based on patient-level medication profiles generated by participating pharmacists, and follow-up data will be collected without knowledge of allocation status in an independent and blinded fashion. All statistical analyses will be conducted by an independent statistician also masked to allocation status.

Covariates that will be collected include age, sex, and self-reported medical diagnoses. Using medication profiles, we will also be able to generate a previously validated measure of comorbidity, the Chronic Disease Score. This measure has been previously demonstrated to provide valid and reliable risk adjustment for comorbidity or case-mix, and it is able to predict long-term morbidity, hospitalization, mortality, and health care utilization [26].

The time period chosen for outcome assessment (6-months) was selected as the vast majority of HF patients (over 80% [10]) are seen at least every 6 months and a poll of general internal medicine specialists and cardiologists at the University of Alberta confirmed that most IHD patients are also seen within this same time period. Data collation, quality assurance, and statistical analyses will be carried out at the EPICORE Centre.

### Statistical analyses

Although the physician will be the unit of allocation, the patient is the unit of analysis and causal inference. This is justified by the anticipated small design effect, and the fact we expect that the outcomes for individual patients to be clinically and statistically independent of each other – because each intervention is itself both patient- and condition-specific. The main analysis will be a comparison of the proportion of all patients who successfully achieve the primary outcome ("improved" prescribing of efficacious therapies, as described above) at 6-months. This will be tested using the chi square statistic. There will be no planned interim analyses, and we will consider a p-value <0.05 to be statistically significant. Secondary analyses will compare the proportions of patients who successfully achieve the primary outcome in each of the two cardiovascular conditions (HF and IHD), to determine whether observed effects are consistent across different disease states. Two prespecified subgroups (male vs. female and age less than 70 years vs. 70 years of age and older) will also be considered. Secondary outcomes will be studied in an analogous fashion, and will be considered only exploratory in nature, and as such, comparisons will be made without corrections for multiple testing.

In order to investigate what factors are associated with changes in the primary outcome (our dependent binary variable), and to control for the possibility of potential imbalances in patient-level characteristics induced by our randomization scheme, multivariable logistic regression analyses will be used to examine those variables that are deemed to be clinically important (i.e., age, sex, diabetes status) or that differ statistically at a p-value <0.10 between experimental arms. In addition, to examine the remote possibility of "cluster-associated" study design effects, two secondary sensitivity analyses will be considered: first, the main analysis will be repeated using the physician as the unit of analysis [2,23,24]; and second, the aforementioned logistic regression models will be re-analyzed using generalized estimating equations to control for the potential lack of statistical independence among patients treated by the same study physician [2,23,24].

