**Methods (study design):**

A pragmatic single-centre cluster randomized controlled trial comparing an opinion leader-based intervention to usual care for patients with HF or IHD. Randomization will be clustered at the level of the primary care physician; as the design effect is anticipated to be negligible, the unit of analysis will be the patient. Patients with HF or IHD (not receiving ACE inhibitors or statins, respectively) will be recruited from community pharmacies and allocated to intervention or usual care based on the randomization status of their primary care physician. The primary outcome is improvement in prescription of proven efficacious therapies for HF (ACE inhibitors) or IHD (statins) within 6 months of the intervention.

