### Allocation to experimental arms

Simple randomization will occur at the level of the primary care physician, before patient recruitment and enrollment begins, using a computer-generated sequence with allocation concealment. Each participating physician will be randomly allocated to intervention or control arm for HF; physicians allocated to intervention for HF will be automatically assigned to the control arm for IHD, and vice versa. This design prevents "contamination" within an individual physicians' practice (e.g., having one intervention HF patient and one control HF patient), while simultaneously increasing study efficiency (i.e., physicians can contribute patients to both the HF and IHD arms of the study, thus potentially reducing the overall number of physicians required). Furthermore, no one physician will be permitted to contribute more than 5 patients to the study, to minimize any issues related to the potential for physician-level clustering of study outcomes [23,24].

That said, this might be considered a form of "cluster" randomization [2,23,24]. However, on a population-wide basis we anticipate that most regional physicians will contribute no patients, and the majority of physicians will contribute no more than 1 study patient. This has been the case in previous studies we have recently undertaken using similar recruitment and allocation methods [19,25]. Furthermore, by our study design, no physician will be able to contribute more than 5 patients to the study as a whole. Therefore, the "design effect" should be negligible, particularly since previous studies have demonstrated that important cluster effects do not come into play until the physician-to-patient ratio exceeds 1-to-5, and we expect our ratio to be close to 1-to-1; thus, all sample size and analytic considerations will be based on the patient as the unit of analysis and the unit of causal inference [23-25].

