### Outcome measures

The primary outcome measure will be the "improvement" of prescribing for efficacious therapies in patients with a chronic cardiovascular disease within 6 months of the intervention. By study design, none of the study patients will be taking the medications of interest. For HF, starting any ACE inhibitor or angiotensin receptor blocker will be considered a positive outcome. For IHD, starting any statin will be considered a positive outcome. For the primary outcome all positive study-related medication changes will be pooled for an overall estimate of effect, compared with usual care controls.

The main secondary outcomes will be condition-specific "improvement" in prescribing after 6 months. In addition, we will attempt to assess optimization of dosage for each of the medications prescribed (i.e., ACE inhibitors or angiotensin receptor blockers and statins). We will also evaluate patient adherence (using prescription refill rates based on dispensing records) and examine the potential influence of age and sex on outcomes.

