### Sample size considerations

Using surveys of physicians and policy-makers, we determined that the "minimal" clinically important difference for this particular intervention to be considered both useful (and perhaps) fundable on an ongoing basis, was a 20% improvement over and above usual care. By design, use of any of the study medications at baseline will be zero. After 6 months, we assume no more than 10% of control patients will have started a study medication. Acknowledging that a 20% absolute increase in the primary outcome (starting a study medication, either an ACE inhibitor or angiotensin receptor blocker [HF] or a statin [IHD]) would be a clinically important effect size, setting the α error rate at 0.05 (2-sided), and the β error at 0.20 (power 80%), a total sample size of 140 will be required. Allowing for losses to follow-up, the ability to examine each of the conditions separately, and the possibility of a very small design effect associated with patient clustering, the total sample size has been adjusted upwards to 160 patients.

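### Physicians are randomised, but the primary test is a patient-level chi-square that ignores this; the error is small at the forecast cluster size and grows if few physicians supply most patients

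*Protocol article*

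**What the plan says.** Under Allocation to experimental arms, the protocol sets the level of randomisation: "Simple randomization will occur at the level of the primary care physician, before patient recruitment and enrollment begins". The allocation is mirrored across conditions: "physicians allocated to intervention for HF will be automatically assigned to the control arm for IHD, and vice versa". Under Outcome measures, the two conditions are combined: "For the primary outcome all positive study-related medication changes will be pooled for an overall estimate of effect".

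Statistical analyses then sets the patient as the unit: "Although the physician will be the unit of allocation, the patient is the unit of analysis and causal inference". Of the primary comparison it says: "This will be tested using the chi square statistic". The abstract gives the reason: "as the design effect is anticipated to be negligible, the unit of analysis will be the patient". Three supports are offered:

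- Physicians are expected to supply close to one patient each, with a cap of five.
- A threshold claim is made, namely that "important cluster effects do not come into play until the physician-to-patient ratio exceeds 1-to-5".
- Outcomes are expected to be independent because each letter is specific to a patient and a condition.

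Two cluster-aware analyses are listed, both as secondary sensitivity analyses that are to be considered. One repeats the main analysis with the physician as the unit. The other refits the covariate-adjusted logistic models by GEE.

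**The concern.** The outcome is a prescribing decision, and patients of one physician share the person who makes it. A letter tailored to each patient does not remove that shared tendency. Nor is there a cluster size below which clustering switches off: with a positive ICC, the variance of an arm proportion rises as soon as some physicians supply more than one patient to that arm.

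The mirrored allocation adds a second dependence. A physician who supplies both conditions has patients in both arms of the pooled comparison, so the two arms are not independent samples. This works in the opposite direction to ordinary clustering.

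At stake is the trial's one confirmatory p-value. Its true error rate depends on how many patients each physician supplies and in which condition, and the plan forecasts this without controlling it beyond the cap. In the condition-specific comparisons, all of a physician's patients are in one arm, so nothing offsets the clustering.

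**Working it through.** **Inputs from the protocol.** Start rates 10% and 30%, two-sided alpha 0.05, power 80%, 140 patients raised to 160 (Sample size considerations). Forecast ratio close to 1-to-1 and a cap of 5 (Allocation to experimental arms).

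**Assumptions.** ICC 0.05, 0.10 and 0.20, since none is given; equal allocation.

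**Step 1: the plan's own figure.** Per arm, n = [1.96·√(2·0.2·0.8) + 0.842·√(0.1·0.9 + 0.3·0.7)]² / 0.2² = 61.6, so 62 per arm and 124 in total. With continuity correction, n′ = (61.6/4)·[1 + √(1 + 4/(61.6·0.2))]² ≈ 71.3, so 72 per arm and 144 in total. The stated 140 is within 3% of this, so it is reproduced by a formula that treats patients as independent.

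**Step 2: clustering when each physician supplies one condition.** Design effect DE = 1 + (m* − 1)·ICC, where m* = Σm²/Σm is the size-weighted mean. Actual alpha of the unadjusted test = 2·[1 − Φ(1.96/√DE)].

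- One patient per physician: DE = 1, alpha 5.0%. There is no error.
- Close to the forecast: 100 physicians with 1 patient, 20 with 2 and 4 with 5 (160 patients, mean 1.29). Then m* = (100 + 80 + 100)/160 = 1.75, DE = 1.04 / 1.075 / 1.15, and alpha = 5.4 / 5.9 / 6.8%.
- All at the cap: 160/5 = 32 physicians, DE = 1.20 / 1.40 / 1.80, alpha = 7.4 / 9.8 / 14.4%.

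**Step 3: mirrored allocation, pooled test.** For a physician with m patients in each condition, DE = 1 + (m − 1)·ICC_within − m·ICC_between. With m = 5 and both ICCs 0.10, DE = 1 + 0.4 − 0.5 = 0.90 and alpha is about 3.9%: conservative. That example uses 10 patients per physician, which only the per-condition cap under Study design allows. The Exclusion criteria and Allocation sections set 5 overall.

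**Step 4: simulation.** Beta-binomial prescribing tendency with mean 10% in both arms, a coin flip per physician with mirrored arms, 160 patients, uncorrected chi-square, 8,000 replicates:

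| Pattern | ICC 0.05 | ICC 0.10 | ICC 0.20 |
|---|---|---|---|
| Mean 1.29 per physician, one condition each | 5.4% | 5.4% | 6.6% |
| All at 5, one condition each | 7.1% | 9.4% | 14.2% |
| All at 5, conditions mixed at random, same tendency in both | 5.2% | 5.1% | 4.9% |
| All at 5, conditions mixed at random, unrelated tendencies | 5.6% | 7.3% | 9.9% |

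The offset in row three therefore needs a physician's tendency to carry over from one condition to the other. At about 2.1 patients per physician in one condition, two separate runs gave 6.3–6.4%, 6.7–7.4% and 8.7–9.8%.

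**Step 5: condition-specific tests.** With all physicians at the cap and conditions mixed at random, the chi-square within one condition has a type I error of about 6–9% over the ICC range; one run reached 10% at ICC 0.20. The figure is below row two because the five patients are shared between conditions.

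**Step 6: power of a test with correct variance.** Exact chi-square power for 10% against 30% at the effective sample size:

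| DE | 160 patients (per arm) | With 10% loss |
|---|---|---|
| 1.0 | 90% (80) | 87% |
| 1.2 | 84% (67) | 80% |
| 1.4 | 79% (57) | 73% |
| 1.8 | 68% (44) | 63% |

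**The case against.** The choice is disclosed and argued, and under the plan's own forecast it does little harm. The setting has about 800 physicians for 160 patients, and most contributors are expected to supply no more than one. At that pattern type I error is about 5–7%, and the upper end needs an ICC of 0.20. The 14% figure needs 32 physicians, all at the cap, each supplying one condition, with that same high ICC; this contradicts the forecast. The threshold sentence speaks of important effects, not of zero effect, and cites sources not available here. Two cluster-aware analyses are planned, clustering is named among the reasons for going from 140 to 160, and secondary outcomes are declared exploratory. All of this stands, and it limits the size of the problem.

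It does not remove the mismatch. The forecast is not a constraint. The planned GEE refits the covariate-adjusted models, not the main comparison. An analysis by physician is not well defined for the pooled comparison when one physician sits in both arms. Both analyses are only to be considered, so the chi-square decides.

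A reader might infer that the primary test is always too liberal. It is not: mixed conditions can bring it to nominal or below. A reader might also infer that planned confidence intervals are too narrow. The protocol names none, so this applies only to an interval computed in the same way.

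**Conclusion.** The point holds in a limited form. The primary test does not match the unit of randomisation, and neither the tailored letters nor a 1-to-5 threshold justifies treating patients of one prescriber as independent. For an assumed ICC of 0.05–0.20, true type I error of the pooled test is:

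- about 5–7% near the forecast;
- about 7–14% if all physicians reach the cap of 5 in one condition;
- near nominal or conservative if physicians supply both conditions with a shared prescribing tendency.

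The exploratory condition-specific tests stay inflated, at about 6–9% at the cap with mixed conditions.

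The documents do not support saying that the trial ignores clustering, or that the primary result would be badly wrong under the recruitment it expects. Nor do they support the comforting reading that 80% power survives in any case: it does so only if the design effect is about 1.2 or less after 10% loss. The ICC range and the cluster-size patterns are assumptions; only the forecast and the caps come from the protocol.

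**What to change.** Make one cluster-aware test primary:

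- a GEE for starting a study drug on arm and condition, clustered on physician, with small-sample-corrected robust standard errors; or
- a randomisation test that re-draws each physician's HF/IHD assignment as it was made.

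Both handle ordinary clustering and the presence of one physician in both pooled arms. Use the same approach for the condition-specific comparisons. Keep the chi-square as a supportive analysis. Delete the independence and 1-to-5 justifications, and state the assumed ICC and cluster-size distribution. Reconcile the cap of five per condition under Study design with the cap of five overall elsewhere, because it sets the largest possible cluster.

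The cost is analysis wording and one analysis not yet specified, since the planned GEE is covariate-adjusted. Precision falls slightly: if physicians supply about one patient each, almost nothing is lost. If recruitment concentrates in few physicians, power drops as in the last table (79% at a design effect of 1.4 and 68% at 1.8 with all 160 patients). The protocol should say that its 80% depends on clustering being small.

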### Objectives

This study has three main objectives:

1. To determine whether evidence summaries generated and endorsed by local opinion leaders can increase the prescription of efficacious therapies for patients with HF or IHD.

2. To compare the effectiveness of the proposed intervention with two different conditions, to begin to understand the potential for generalizability across different diseases and conditions.

3. To evaluate whether distribution of local opinion leader endorsed evidence summaries, through community pharmacies, is a viable quality improvement tool within the constraints of current healthcare delivery systems.

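### Objective 2 asks whether the effect differs between HF and IHD, but the analysis section only compares arms within each condition and names no between-condition contrast

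*Protocol article*

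**What the plan says.** Under Objectives, the second of three main objectives is "To compare the effectiveness of the proposed intervention with two different conditions", as a first step towards learning whether the approach generalises.

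Under Statistical analyses, the secondary analyses compare the proportions reaching the primary outcome in HF and in IHD, "to determine whether observed effects are consistent across different disease states". The chi-square test and p<0.05 are set out for the main analysis. Secondary outcomes are to be handled in the same way, as exploratory and without multiplicity correction. The logistic models serve to find factors associated with the outcome and to adjust for imbalance. Age, sex and diabetes are the named covariates; condition is not among them and no arm-by-condition term appears. The generalized estimating equations analysis repeats those models with allowance for clustering.

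On age and sex the section says only: "Two prespecified subgroups (male vs. female and age less than 70 years vs. 70 years of age and older) will also be considered".

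Under Sample size considerations, the planning values are "we assume no more than 10% of control patients will have started a study medication" and "a 20% absolute increase in the primary outcome". The total of 140 is then raised to 160, in part so that the conditions can be looked at one by one.

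**The concern.** A comparison of effectiveness between conditions concerns the difference between two treatment effects. Comparing arms within HF, and again within IHD, estimates each effect but gives no measure of how far apart they are or how precisely that is known. Comparing outcome proportions in HF with those in IHD would not contrast effects either.

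The risk lies in interpretation. With about 80 patients per condition, each within-condition test has modest power. A result that is significant in one condition and not in the other is then common even when the true effects are equal. Reported under Objective 2, it could be taken to mean that the intervention works for one disease and not the other.

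**Working it through.** **Inputs from Sample size considerations.** Control 10%, intervention 30%, two-sided α 0.05, power 80%, total 140 before adjustment and 160 after. **Assumed, because not given:** an even HF/IHD split, 1:1 arms within condition (40 per arm per condition), and independent tests.

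**The plan's own figure.** "setting the α error rate at 0.05 (2-sided), and the β error at 0.20 (power 80%), a total sample size of 140 will be required". The usual two-proportion formula gives

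n = [1.96·√(2·0.2·0.8) + 0.842·√(0.09 + 0.21)]² / 0.2² = 61.6, so 62 per arm (124 in total).

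With the continuity correction it is 72 per arm (144 in total), within 3% of 140. The planning values are therefore taken as read.

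**Power within one condition, 40 per arm.** The normal approximation gives Φ[(0.2·√40 − 1.96·0.566)/0.548] = Φ(0.285) = 61%. Exact enumeration of the uncorrected chi-square test gives 63.2%; with continuity correction it is 49.4%.

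**Disagreement in significance when the true effect is identical.** With power π in each condition:

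- One significant, one not: 2π(1 − π) = 2·0.632·0.368 = 46.5%.
- Both significant: 0.632² = 40.0%. Neither: 0.368² = 13.5%.
- With the continuity-corrected test: 2·0.494·0.506 = 50.0%.
- With 140 evaluable patients split 70/70 (exact power 56.5%): 49%.

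**Dependence on the common true effect** (control 10%, 40 per arm per condition, 400,000 simulated trials):

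| True effect in both conditions | Power per condition | Tests disagree |
|---|---|---|
| 0 points | 6% | 11% |
| 10 points | 25% | 37% |
| 15 points | 44% | 49% |
| 20 points | 63% | 47% |
| 30 points | 90% | 18% |

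**Dependence on the HF/IHD split of 160** (20-point effect, exact): 64/96 gives 49%, 48/112 gives 54%, 40/120 gives 59% and 32/128 gives 63%.

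**A direct contrast of the two risk differences, 40 per cell, clustering ignored.**

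- Standard error of one risk difference: √[(0.09 + 0.21)/40] = 0.0866.
- Standard error of their difference: √2·0.0866 = 0.1225, so the 95% CI is ±1.96·0.1225 = ±24 points.
- False signal of a difference when both effects are 20 points: about 5.5% in simulation.
- Power for 20 points against 0: standard error √[(0.09 + 0.21 + 0.09 + 0.09)/40] = 0.1095, and Φ(0.2/0.1095 − 1.96) = 45%.

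**Why these precision figures are best case.** Under Allocation to experimental arms, group A physicians are intervention for HF and control for IHD, and group B the reverse. Writing A and B for the groups' outcome proportions,

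(A_HF − B_HF) − (B_IHD − A_IHD) = (A_HF + A_IHD) − (B_HF + B_IHD).

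The contrast is thus a comparison wholly between the two physician groups. A physician's general tendency to prescribe does not cancel from it, so clustering widens the interval. If most physicians contribute one patient, as the protocol expects, the widening is small.

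**The case against.** The strongest reply is that the faulty rule is not in the document. The protocol speaks of observed effects being consistent; it does not say that one significant and one non-significant result will be called inconsistent. A reader might infer that the trial, run as written, would wrongly report a difference in nearly half of cases. The text does not support that. The 46.5% belongs to a reading rule that the protocol leaves open, although p<0.05 is the only criterion it states for judging a result. Nor does the figure hold for every identical effect, as the table shows.

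A reader might also extend the point to age and sex. The protocol names those subgroups without a method, so separate testing there would be a guess.

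It can further be said that an interaction term is detail for an analysis plan that is not shown, and that these analyses are exploratory. The first holds only in part: the article itself fixes both the within-condition comparison and the inference to be drawn from it, and the two do not match. The second lowers the weight of the point. The exploratory label excuses the lack of multiplicity correction, but it does not turn two within-condition comparisons into a comparison between conditions.

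Finally, the contrast is no cure for a small sample. By the figures above it would miss a 20-against-0 difference about 55% of the time. That stands, and should be stated with the result.

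**Conclusion.** The point holds as a mismatch between a main objective and its stated analysis. Objective 2 needs an estimate of the difference between the HF and IHD effects, and the plan provides none.

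If consistency were judged by agreement of the two tests at p<0.05, equal effects at the planned size would give split results in 46.5% of trials (50% with continuity correction). This assumes an even split, 1:1 arms and independent tests. Independence is approximate, since one physician can contribute to both conditions. Uneven splits raise the figure; common effects well away from 15 to 20 points lower it. A direct contrast would mislead in about 5.5% under the same equal-effect assumption.

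The consequence is confined to the conclusion on generalisability. The pooled primary comparison does not depend on it.

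**What to change.** For Objective 2, specify an arm-by-condition contrast, reported as the difference between the HF and IHD risk differences with a 95% CI that accounts for physician clustering. Present the condition-specific estimates descriptively, and base any statement that the effects are consistent or different on the contrast and its interval.

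State in advance that it is imprecise: at best about ±24 points, with about 45% power for 20 points against none, and somewhat worse with clustering because the contrast lies wholly between physicians. A non-significant contrast should therefore not be reported as proof of consistency.

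If the age and sex results are to be read as effect modification, use the same form of contrast there.

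The cost is a change of wording and one additional estimate, with no new data or patients. The conclusion on generalisability will be more modest.

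### Beyond age, sex and diabetes status, covariates enter the secondary logistic and GEE models only on a baseline p<0.10 test, so condition and the Chronic Disease Score would usually be left out

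*Protocol article*

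**What the plan says.** All references are to the Methods of the protocol article.

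- **Main analysis (Statistical analyses).** The proportions achieving the primary outcome are compared without adjustment: "This will be tested using the chi square statistic".
- **Adjusted models (Statistical analyses).** Multivariable logistic regression follows. One aim is to explore which factors go with the outcome. The other is "to control for the possibility of potential imbalances in patient-level characteristics induced by our randomization scheme".
- **Covariates (Statistical analyses).** The rule has two halves. The first is fixed: "those variables that are deemed to be clinically important (i.e., age, sex, diabetes status", where the bracket closes. The second depends on the data: "or that differ statistically at a p-value <0.10 between experimental arms".
- **GEE (Statistical analyses).** As a sensitivity analysis for clustering, "the aforementioned logistic regression models will be re-analyzed using generalized estimating equations", so the GEE models inherit whichever covariates were selected.
- **Comorbidity (Study procedures and data collection).** "Using medication profiles, we will also be able to generate a previously validated measure of comorbidity, the Chronic Disease Score". The same paragraph credits the score with "valid and reliable risk adjustment for comorbidity or case-mix".

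Neither the Chronic Disease Score nor condition is in the fixed half of the rule.

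**The concern.** The test-driven half of the rule serves neither aim of the model. A difference between arms does not show that a variable is associated with starting treatment. For control of imbalance, what matters is how far a variable is out of balance combined with how strongly it predicts the outcome, and a p-value threshold sees only the first. A strong predictor with moderate imbalance stays out, while an irrelevant variable that differs by luck comes in.

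Two omissions stand out. The protocol singles out the Chronic Disease Score as a case-mix measure and then makes its use depend on a chance test. The primary outcome pools HF and IHD, which involve different drugs, and physicians randomised to intervention for one condition become controls for the other. The split of conditions across arms is therefore a product of the randomisation scheme, which is the kind of imbalance the model is meant to handle.

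At stake are the precision and full prespecification of the adjusted estimate and of its GEE counterpart, the patient-level analysis that allows for clustering.

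**Working it through.** **Inputs.** From Sample size considerations: 10% of controls start a study medication, a 20-point absolute increase (so 30%), two-sided alpha 0.05, power 80%, 140 patients raised to 160. Equal arms of 80 are an assumption, since no ratio is stated. The covariate rule is from Statistical analyses.

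**1. The plan's own figure.**
- Pooled formula: n = [1.96·√(2·0.2·0.8) + 0.842·√(0.1·0.9 + 0.3·0.7)]² / 0.2² ≈ 61.6, so 62 per arm, 124 in total.
- With continuity correction: 72 per arm, 144 in total.
- Unpooled with continuity correction: 69 per arm, 138 in total.

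The stated 140 lies between the two corrected figures, so the sample size is not at issue.

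**2. How often a covariate passes.** Under randomisation a given covariate passes p<0.10 about 10% of the time, so one that is not fixed is left out in about 90% of trials. For k independent candidates, P(at least one enters) = 1 − 0.9^k. The protocol does not give k, so a range is shown:

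| k (assumed) | P(at least one enters by chance) |
|---|---|
| 1 | 10% |
| 3 | 27% |
| 5 | 41% |
| 10 | 65% |

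**3. How much imbalance is ignored.**
- Continuous covariate, 80 per arm: 1.645·√(2/80) = 0.26 SD.
- Binary covariate with 50% prevalence: 1.645·√(2·0.25/80) = 0.13, or 13 percentage points.

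Illustration for condition, assuming 80 HF and 80 IHD patients, with 55% of each belonging to physicians allocated to HF intervention. The intervention arm then has 44 HF and 36 IHD patients (55% HF), and the control arm has 36 HF and 44 IHD (45% HF). That 10-point difference is below 13 points, so condition would not enter.

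**4. What the omission costs.** Simulation of 6,000 trials per scenario: 160 patients, equal arms, 10% vs 30% (or 10% in both arms under the null), with one standard-normal covariate standing in for the score. Its odds ratio per SD is assumed, because the protocol gives none. The models contain arm and, where included, that covariate, with no clustering.

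| OR per SD (assumed) | Power, always adjusted | Power, p<0.10 rule | Null rejection, always | Null rejection, rule |
|---|---|---|---|---|
| 1.5 | 90.5% | 89.8% | 3.8% | 3.6% |
| 2.0 | 91.6% | 90.3% | 3.9% | 3.7% |
| 3.0 | 93.1% | 90.5% | 4.4% | 3.9% |

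The covariate entered under the rule in 9.7% to 10.5% of trials. The loss is about 1 to 3 points of power. The rule's null rejection rate stays below 5% throughout.

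**5. Events available.** 80·0.10 + 80·0.30 = 32.
- Arm plus the three fixed covariates: 32/4 = 8 per parameter.
- With one chance covariate added: 32/5 = 6.4.
- Arm plus the five proposed covariates: 32/6 ≈ 5.3.

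If the intervention had no effect, 160·0.10 = 16 events would be expected, and the last figure falls to 16/6 ≈ 2.7.

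**The case against.** The strongest defence is that the rule is limited, stated in advance and close to harmless. Age, sex and diabetes status enter whatever the baseline table shows. The test uses baseline variables and not outcomes, the statistician is masked to allocation, and the primary test does not use the model. All of this stands, and it sets the limits of the point.

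A reader who sees only the second half of the rule might infer that the whole adjustment set is chosen by testing, or that the headline result or its error rate is at risk. The text does not support the first: three covariates are fixed. It does not support the second either: the main analysis is an unadjusted chi-square, and the simulation shows no inflation.

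Four further objections carry some weight.

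- The documents do not show that the Chronic Disease Score predicts starting an ACE inhibitor, angiotensin receptor blocker or statin. They say that it predicts morbidity, hospitalisation, mortality and utilisation. The odds ratios above are therefore assumptions. But the protocol itself offers the score for risk adjustment, and a between-arm test would not settle its prognostic value.
- Physicians are randomised before patients are identified and consented, so patient-level differences need not be pure chance, and the 10% figure describes chance only. This does not rescue the test, which still ignores prognosis.
- The baseline tests could be mis-sized under physician clustering, but no size can be given, and the protocol expects close to one patient per physician. Nothing here rests on it.
- The fixed five-covariate model uses more parameters than the current rule does with one chance entry (6 against 5). That is a real cost and belongs with the fix.

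**Conclusion.** The point holds as a narrow one. Beyond age, sex and diabetes status, entry to the secondary logistic models and their GEE refit depends on a baseline p<0.10 test. That test selects on imbalance, so condition and the Chronic Disease Score would be left out in about 90% of trials if differences arise by chance. The protocol states this rule outright, so it is not a detail left to an analysis plan.

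The size is small: about 1 to 3 points of power in the adjusted analysis, for assumed odds ratios of 1.5 to 3.0 per SD, equal arms and no clustering. The 65% chance of at least one stray covariate should not be quoted alone, because it needs 10 candidates. It is 27% with 3 and 41% with 5. The case for change is that a poor selection method can be replaced by a prespecified one at almost no cost, not that the trial's conclusion is in danger.

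**What to change.** Delete the p<0.10 criterion in Statistical analyses. State instead that the adjusted logistic models and the GEE re-analysis will include condition (HF or IHD), age as a continuous variable, sex, diabetes status and the Chronic Disease Score, whatever the baseline table shows.

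The cost is one sentence. Condition is known at recruitment, age, sex and self-reported diagnoses are already collected, and the score comes from medication profiles already obtained. Sample size, alpha and the primary test do not change.

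The downside is model size: treatment plus five covariates on about 32 expected events, about 5 per parameter, and fewer if the effect is smaller than assumed. The list should therefore not be extended further.
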